#### Diet

For the assessment of dietary intake, a food frequency recall is used, which has been validated previously in a survey [39].

#### Quality of life

To assess quality of life, the validated German KINDL^R^-questionnaire [40,41] with six dimensions ("physical well-being", "emotional well-being", "self-esteem", "friends", "family" and "everyday functioning (school)") is being used. The subscales of these six dimensions are combined to a total score. Furthermore, an additional sub-scale, developed specifically to assess the quality of life of overweight children, is being used, which consists of a filter question and six items. The reliability and validity of this questionnaire have been described elsewhere [41].

In addition, a standardized questionnaire that is supposed to be completed by the parents on the day of admission is being used to obtain demographic information as well as obesity-related health history of first degree family members.

### Follow-up (Visits 3 to 7)

#### Visits 3, 4 and 5

Prior to the first follow-up examination, which takes place 6 months after the start of the program (Visit 3), study investigators contact the general practitioners by telephone to inform them about the study procedures and to obtain agreement on carrying out the upcoming follow-up examinations. The general practitioners are asked to complete and return a standardized examination sheet including anthropometric measurements (body weight, height and waist circumference), blood pressure and Tanner stage as well as comorbidities and the current use of medication.

In addition, study investigators contact the children prior to each visit (6 months, 1 year and 2 years after the start of the intervention) to remind them of the upcoming examination and to enquire about possible address changes. The children are requested to complete the questionnaires, previously sent by post, and to return them using the provided prepaid envelope as well as to visit their general practitioner for the follow-up examination. If both the questionnaires and the examination sheet are returned to the study centre, the children will receive an allowance of 10 Euros.

#### Visits 6 and 7

For the 5 and 10 year follow-up examinations, the children are invited to visit the study centre at the *Department of Prevention, Rehabilitation and Sports Medicine, Technical University of Munich*, where the same measurements as at baseline (Visit 1) are planned to be obtained (except for DNA and family history). Children, who are not able to visit the study centre, have blood samples taken by their general practitioner in addition to the basic examination as carried out for the previous follow-up examinations. The blood parameters analysed are fasting HDL, LDL, total cholesterol, triglycerides and glucose. The allowance for each of this visit is 20 Euros.

At all visits, children whose documents have not been returned to the study center are contacted by telephone, repeatedly if necessary, in order to collect the missing documents. If children wish to withdraw from the study in spite of efforts to motivate them to continue participating, study investigators fill out an official drop out sheet.

### Statistical considerations

Associations between polymorphisms in adiposity-relevant genes (*FTO, MC4R, TMEM-18*) and changes in BMI(-SDS) from the start to the end of the intervention, will be assessed using analysis of covariance (ANCOVA) models comparing mean changes in BMI(-SDS) between the two groups of homozygous and the group of heterozygous children adjusted for age, sex and baseline weight. A two-sided level of significance of α = 0.05 will be used. For pairwise group comparisons, two-sample t-tests will be conducted using a Bonferroni-adjusted level of significance of α* = 0.0167.

Middle and long-term associations between genes and measures of interest such as weight change, physical fitness and physical activity will analogously be analysed in an explorative manner. Linear regression models including all relevant genes plus baseline weight, age and sex will be fit into estimate predictive models for the expected short and long-term weight changes. Predictive accuracy of the models and most relevant genes will be assessed using re-sampling methods (e.g. bootstrap) [42]. To estimate the influence of genes on relevant measures over time, a mixed model will be fit to account for multiple measures in the same participants. Missing values will be replaced using multiple imputation methods based on observed values with varying assumptions. Differences in the results obtained by different imputation strategies will be reported and discussed.

With a sample size of 1,500 children the study is sufficiently powered to detect significant differences in all pairwise comparisons between allele groups on an adjusted two-sided level of significance of α* = 0.0167, if the true difference in means is at least half of the common standard deviation translating to an effect size of 0.5 (power > 90% for each pairwise comparison). The sample size calculation is based on the assumption that the distribution of alleles leading to the smallest subgroups will be 70%, 25% and 5%, hence the smallest sample sizes for pairwise comparisons will be 375 versus 75 children. Sample size estimation was conducted for a two-sample t-test with unequal group sizes using the software nQuery (Version 7.0).

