#### Primary endpoint

The associations between polymorphisms in adiposity-relevant genes (e.g. *FTO, MC4R, TMEM-18*) on the changes in BMI and BMI-SDS after a controlled lifestyle intervention (4 to 6 weeks) in overweight and obese children and adolescents.

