### Intervention

The rehabilitation clinic is primarily focused on inpatient treatment for childhood overweight and obesity which typically lasts for 4 to 6 weeks. The duration of the stay depends on health insurance allowance and the severity of obesity. Typically the children are referred to the clinic for 4 weeks and in case of severe obesity or comorbidities they have the opportunity to extend the program. The standardized multimodal program focuses on a calorie restricted balanced diet, an increase in physical activity and behavioral counseling. It is conducted by an interdisciplinary team of pediatricians, exercise physiologists, dieticians, psychologists and pedagogues according to German guidelines for inpatient weight-loss programs (AGA, Arbeitsgemeinschaft Adipositasim Kindes- und Jugendalter) [31].

The children are offered an optimized balanced diet prepared according to current guidelines (30%, 15% and 55% of the total energy content from fat, proteins and carbohydrates, respectively), with an allowed energy intake of 1,250-1,800 kcal^a ^per day, depending on height and sex (Table 2) [32]. The components of the intervention program are shown in Table 3. In brief, the children are required to participate in theoretical and practical lessons on healthy eating, physical activity and behavior change skills based on the cognitive-behavioral theory. The exercise therapy consists of approximately 10 h of organised physical activity per week,^b ^in addition to 6 hours of recreational exercise.

**Table 2 T2:** Calculation of the allowed energy intake based on body height and sex

Boys		Girls	
Height [cm]	Energy intake per day [kcal]	Height [cm]	Energy intake per day [kcal]
≤ 145	1250	≤ 155	1250
146-170	1500	156-180	1500
≥ 171	1800	≥ 181	1800

**Table 3 T3:** Components of the inpatient weight-loss program

Intervention component	Items	Description	Aims	Frequency/Dose
**Structured physical activity (10 h/week)**	Therapeutic sports	Different types of outdoor activities such as ascending stairs, road running and cross country runs etc.	Endurance training according to individual abilities	2x/week à 60 min
	
	Swimming	Lane swimming ~1.000 m	Endurance training; Learning/improving swimming technique	1x/week à 50 min plus the 6 km walk to the pool (~3 km downhill, 3 km uphill)
	
	Group sports	Different physical activities (e.g. ball games, dancing and gymnastics)	Focus on playing and having fun	1x/week à 45-90 min
	

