#### Physical examination

Body height is measured barefoot to the nearest 0.5 cm by a rigid stadiometer. Body weight is measured with minimal clothing to the nearest 0.1 kg by a digital scale (Visit 1 and 2: *Tanita BC-420 P MA Profi, Tanita Europe B.V*., Hoofddorp, The Netherlands; Visits 3-7: calibrated scale). Waist circumference is measured on bare skin by tape to the nearest 0.1 cm midway between the lower rib margin and the iliac crest in standing position after normal exhalation with a non-stretchable tape measure. Blood pressure is measured at the right brachial artery in the fossa cubitalis after the children have been resting for 5 min in supine position by using a validated protocol [33]. Pubertal development is determined according to Marshall and Tanner [34,35]. Data on the medical history are documented including current medication and comorbidities (orthopedic complications, attention deficit (hyperactivity) disorders, thyroidal diseases, asthma, metabolic diseases, psychological diseases, acute diseases). All inpatient examinations and assessments are conducted by trained medical staff according to standardized procedures.

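### The primary ANCOVA of BMI(-SDS) change adjusts for weight but not height, so it lacks the baseline value of its own outcome, and the pairwise t-tests use no covariates

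*Protocol article*

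**What the plan says.** The Primary endpoint section names change in BMI and in BMI-SDS over the 4 to 6 week inpatient stay, related to polymorphisms such as FTO, MC4R and TMEM-18.

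Statistical considerations then fixes three analyses:

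- **Primary ANCOVA.** Mean changes in BMI(-SDS) are compared "between the two groups of homozygous and the group of heterozygous children adjusted for age, sex and baseline weight", at two-sided 0.05.
- **Pairwise comparisons.** "For pairwise group comparisons, two-sample t-tests will be conducted using a Bonferroni-adjusted level of significance" of 0.0167.
- **Prediction models.** "Linear regression models including all relevant genes plus baseline weight, age and sex" are to give "predictive models for the expected short and long-term weight changes".

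Height is available at baseline. Under Physical examination, "Body height is measured barefoot to the nearest 0.5 cm by a rigid stadiometer", and Table 4 lists anthropometry, including height, at Visit 1. Height also has a role in treatment: Table 2 in the Intervention section is titled "Calculation of the allowed energy intake based on body height and sex".

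**The concern.** An ANCOVA of change normally conditions on the baseline value of the outcome. Here the outcome is BMI or BMI-SDS, but the covariate is weight. Two children of the same age, sex and weight but different height have identical covariate values, yet they start at different BMIs, and the same weight loss gives them different BMI changes. Part of the outcome variation that baseline data could explain is therefore left in the error term.

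The pairwise comparisons go further: as two-sample t-tests they ignore age, sex and weight as well. They are also the comparisons on which the sample size is justified, so improving the ANCOVA covariates does nothing for them unless they are taken from that model.

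What is at stake is precision in the genotype comparisons, particularly those involving the rare homozygotes, whom the sample size assumption puts at 75 of 1,500 children.

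**Working it through.** **1. The plan's own figure.** Inputs from Statistical considerations: 1,500 children split 70%/25%/5%, so 1,050, 375 and 75; difference 0.5 SD; two-sided level 0.05/3 = 0.0167. For 375 versus 75 the noncentrality is 0.5/√(1/375 + 1/75) = 3.95 on 448 degrees of freedom. The noncentral t gives power of 93.9%. The stated figure above 90% is reproduced, and it involves no covariates.

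**2. Why weight alone does not fix baseline BMI.** Illustrative children, both 80 kg:

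| Height | Baseline BMI | BMI change per 1 kg lost |
|---|---|---|
| 150 cm | 80/1.50² = 35.6 | 1/1.50² = 0.44 |
| 160 cm | 80/1.60² = 31.3 | 1/1.60² = 0.39 |

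The same loss moves BMI 12% less in the taller child (0.391/0.444 = 0.879). In a simulation with assumed growth and BMI distributions, age, sex and weight explained about 72% of baseline BMI variance, and about 96% once height was added. Weight plus height therefore approximates baseline BMI closely; weight alone does so only in part.

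**3. What height could be worth.** The document gives no variance components, so the share R² of residual variance (after age, sex and weight) that height explains is an assumption. Standard errors scale by √(1 − R²). Residual degrees of freedom go from 1,500 − 6 = 1,494 (three genotype means plus three covariates) to 1,493. The detectable difference is for the three-group F test at 0.05 with 90% power and only the rare homozygotes differing. Contrast power is for 375 versus 75 at 0.5 SD and 0.0167, with the SD read as the residual SD of the planned ANCOVA.

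| Assumed R² | Standard error falls by | Detectable difference | Power if taken as ANCOVA contrast |
|---|---|---|---|
| 0 | none | 0.422 SD | 94.0% |
| 2% | 1.0% | 0.418 SD | 94.5% |
| 5% | 2.5% | 0.411 SD | 95.1% |
| 10% | 5.1% | 0.400 SD | 96.2% |

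Left as a two-sample t-test, the pairwise comparison stays at 93.9% on every row.

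**4. Is the assumed range reasonable?** Suppose BMI change is weight loss divided by height squared, with loss independent of height. Let c be the coefficient of variation of height at fixed age, sex and weight, and r the mean-to-SD ratio of the loss. Then R² ≈ 4c²r²/(1 + 4c²r²). With c from 3% to 5% and r from 1.5 to 3 (all assumed), R² runs from 0.8% to 8.3%. The simulation in step 2, with BMI change assumed proportional to baseline BMI, gave about 4%. At 0.8% the standard error falls by only 0.4%.

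**5. Bias.** In the same simulation the genotype coefficient was about zero with or without height when genotype was unrelated to height. When genotype was assumed to shift height by 0.5 to 2 cm, the coefficient from the weight-only model moved by roughly 0.01 to 0.04 BMI units, under 0.05 SD. The document says nothing about such a link.

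BMI-SDS was not calculated, because the reference constants are not in the document.

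**The case against.** The best defence is that age, sex and baseline weight is a legitimate prespecified set, that nothing in the section is false or contradictory, and that preferring another prognostic covariate is a matter of taste. Age, sex and weight already carry much of the information on height in children aged 6 to 19. The gain rests on an assumed R² that may be below 1%. Most of this stands, and it is why the point is minor. It does not remove the point: the covariate list is stated explicitly, it leaves out a measured component of the primary outcome, and the pairwise tests discard even the covariates that were chosen.

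Three stronger readings are tempting but unsupported.

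- **That the genotype comparison is biased because height sets the energy allowance.** Energy is assigned by height and sex, not by genotype, and sex is already in the model.
- **That the steps in Table 2 measure the harm.** Boys of 145 and 146 cm are allowed 1,250 and 1,500 kcal per day, or 250 × 28 = 7,000 kcal over four weeks. This is a difference in allowance at a band edge. It is not a difference in energy deficit or in BMI change, since a taller child may also expend more. A linear height term would barely separate these two boys in any case.
- **That the prediction regressions share the defect.** Their stated outcome is weight change, and they include baseline weight. For them height is only an optional candidate predictor, on the ground that it sets the allowance.

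Replacing weight with baseline BMI would be the textbook ANCOVA, but it is more debatable here. The Background section reports that the FTO risk allele is associated with higher BMI, so that covariate is itself linked to the exposure.

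**Conclusion.** The point holds as a modest loss of precision in the primary analysis. The ANCOVA does not account for the baseline value of BMI or BMI-SDS, and the pairwise t-tests account for no baseline value. On an assumed R² of 2% to 10% for height, ANCOVA standard errors would be about 1% to 5% smaller, and the detectable rare-homozygote difference would fall from 0.422 SD to between 0.418 and 0.400 SD. The true size is unknown and could be smaller. No bias is shown, the sample size need not change, and the stated power stands. The change is desirable but not essential.

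**What to change.** Add baseline height to the primary ANCOVA alongside age, sex and baseline weight. Take the three pairwise genotype comparisons as contrasts from that ANCOVA, each at 0.0167, in place of the two-sample t-tests.

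Report two sensitivity analyses: the model as now written (age, sex, baseline weight), and a model with age and sex only. The second is needed because adjusting for baseline body size removes any genotype effect that acts through it. This is already so for weight, and adding height extends it.

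For the prediction regressions, height may be offered as a candidate predictor; nothing requires it.

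The cost is one residual degree of freedom (1,494 to 1,493 with 1,500 children), no new measurements, and two extra models to report.

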**Methods/Design:**

The study involves overweight and obese children and adolescents aged 6 to 19 years, who participate in an inpatient weight-loss program for 4 to 6 weeks. It started in 2006 and it is planned to include 1,500 participants by 2013. The intervention focuses on diet, physical activity and behavior therapy. Measurements are taken at the start and the end of the intervention and comprise blood analyses (DNA, lipid and glucose metabolism, adipokines and inflammatory markers), anthropometry (body weight, height and waist circumference), blood pressure, pubertal stage, and exercise capacity. Physical activity, dietary habits, quality of life, and family background are assessed by questionnaires. Follow-up assessments are performed 6 months, 1, 2, 5 and 10 years after the intervention: Children will complete the same questionnaires at all time points and visit their general practitioner for examination of anthropometric parameters, blood pressure and assessment of pubertal stage. At the 5 and 10 year follow-ups, blood parameters and exercise capacity will be additionally measured.

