**Physical examination**							

Anthropometry*	+	+	+	+	+	+	+

Pubertal stage (Tanner)	+		+	+	+	+	+

Comorbidities/Medication	+	+	+	+	+	+	+

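### Baseline Tanner stage is collected in a cohort that spans puberty, but it is left out of the weight-change prediction models and of any check on the genotype ANCOVA

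*Protocol article*

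**What the plan says.** The abstract describes the cohort as "overweight and obese children and adolescents aged 6 to 19 years". Under Physical examination, "Pubertal development is determined according to Marshall and Tanner". Table 4 schedules the assessment at Visit 1 and at Visits 3 to 7, but not at Visit 2. The Follow-up section also puts Tanner stage on the sheet that general practitioners return.

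The Statistical considerations section then lists covariates for two models:

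- **Primary genotype ANCOVA** (change in BMI and BMI-SDS over the inpatient stay): "adjusted for age, sex and baseline weight".
- **Prediction models** for expected short and long-term weight change: "Linear regression models including all relevant genes plus baseline weight, age and sex". Their accuracy is to be assessed by re-sampling, with the bootstrap as the example.

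Neither list contains pubertal stage, and the article gives no reason. Three further statements limit the point. The pairwise genotype comparisons are two-sample t-tests at 0.0167. The middle and long-term gene associations are to be analysed along the same lines but are called explorative. A mixed model is planned, without a covariate list.

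**The concern.** An age range of 6 to 19 covers children before, during and after puberty, and children of the same age and sex can differ in stage. Maturation bears on growth and body composition, so stage may carry information about weight change that age, sex and baseline weight do not. This matters most over the follow-up of 6 months to 10 years, when many of these children pass through puberty. The protocol makes a related link itself: its section on the role of genes ties an *FTO* variant to BMI at age 7 and to obesity in puberty and later.

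The stated aim is to find determinants of weight loss and weight maintenance. A prediction model for that purpose would normally consider a relevant baseline variable that has already been measured. What is at stake is predictive accuracy in those models and, to a lesser degree, precision in the genotype ANCOVA. The article states both covariate lists, so this concerns a stated choice and not a detail left to an unseen analysis plan.

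**Working it through.** **Inputs from Statistical considerations.** N = 1,500; genotype split 70/25/5%, giving 1,050, 375 and 75 children; effect size 0.5 SD; two-sided level 0.0167 per pairwise test; stated power above 90%.

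**Assumed input.** R²p is the share of variance left after age, sex and baseline weight that baseline Tanner stage would explain. The protocol gives no value. The working range is 0.01 to 0.05, with 0.10 as a more generous case.

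**Step 1. Reproduce the plan's figure.** For 375 versus 75 the noncentrality is 0.5/√(1/375 + 1/75) = 0.5/√0.016 = 3.95. At level 0.0167 this gives power of 94.1% by the normal approximation and 93.9% by the noncentral t. The 1,050 versus 75 comparison gives 96.3%, and 1,050 versus 375 gives more than 99.9%. The stated claim of above 90% holds with no covariate at all.

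**Step 2. Precision gain in the ANCOVA.** The standard error is multiplied by √(1 − R²p). The equivalent number of extra children is 1500/(1 − R²p) − 1500.

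| R²p (assumed) | SE reduction | Extra children |
|---|---|---|
| 0.01 | 1 − √0.99 = 0.5% | 1,515 − 1,500 = 15 |
| 0.05 | 1 − √0.95 = 2.5% | 1,579 − 1,500 = 79 |
| 0.10 | 1 − √0.90 = 5.1% | 1,667 − 1,500 = 167 |

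**Step 3. What this would mean for power.** Suppose the 375 versus 75 comparison were made as a contrast from the ANCOVA, with the effect in SD units after age, sex and weight. The plan does not do this, so these figures are an upper bound on relevance.

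| R²p (assumed) | Power at 0.5 SD | Power at 0.3 SD |
|---|---|---|
| 0 | 93.9% | 48.8% |
| 0.05 | 95.0% | 51.3% |
| 0.10 | 96.1% | 53.9% |

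**Step 4. Cost.** A categorical stage term uses up to 4 degrees of freedom in 1,500 children: 4/1500 = 0.27%.

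**Step 5. Which analyses the gain reaches.** It can reach the ANCOVA and the prediction models. It cannot reach the pairwise t-tests, which carry no covariates and on which the sample size rests. For the mixed model the question cannot be answered, because its covariates are not given.

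**The case against.** The strongest reply is that nothing here is wrong. Age, sex and baseline weight form a coherent prespecified set, and recording a variable does not oblige its use; fitness, diet and medication are recorded too. The primary outcome covers only 4 to 6 weeks, and one of its two forms is already a standardised score. The existing covariates are likely to carry part of what stage would add. The power claim is met without any adjustment. All of this stands, and it is why the point is minor.

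The reply also disposes of several stronger readings that a reader might infer:

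- **Biased genotype estimates.** Genotype is fixed at conception, so pubertal stage cannot cause it and is not a confounder in the usual sense. If stage is unrelated to genotype, leaving it out of a linear model causes no bias. If adiposity genes act partly through maturation, stage is a mediator, and adjusting for it would remove part of the genetic effect. Adjusting for stages recorded at Visits 3 to 7, after baseline, would sharpen that problem.
- **Lost precision in every genotype comparison.** The pairwise comparisons are unadjusted t-tests and would not change.
- **Age entered only as a straight line.** The article does not state the form of the age term.
- **Omission from the mixed model.** No covariates are listed for it, so no omission is shown.

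The objection does not reach the prediction models. Their purpose is accuracy, so a possible mediating role is no reason to exclude a baseline predictor. Their stated scope includes long-term weight change, so the short primary window does not answer the point there. Missing stages are no barrier either, since multiple imputation is already planned.

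**Conclusion.** The point holds as a minor improvement. Two stated covariate lists omit baseline Tanner stage, which is collected in a cohort spanning puberty, and no reason is given. The case is clear for the prediction models. For the genotype ANCOVA it supports a sensitivity analysis only, because the groups are genotypes and not randomised arms, and adjustment can change the estimand as well as the variance.

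The size rests wholly on an assumed R²p. At 1 to 5% the ANCOVA gains the equivalent of about 15 to 79 children. Even at 5%, power for the smallest comparison at the design effect would move only from 93.9% to 95.0%, and only if that comparison were taken from the ANCOVA. The gain for the 4 to 6 week change is probably small. It could be larger over longer follow-up, but the protocol has no figure to show it, and one baseline value describes children moving through puberty only partly. The documents do not support a claim that the primary analysis is invalid or underpowered for this reason.

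**What to change.** 1. Add baseline Tanner stage, as a categorical term, to the prediction models for short and long-term weight change. Use the re-sampling already planned to compare predictive accuracy with and without it, and report the comparison whichever way it falls.
2. Keep the genotype ANCOVA as stated for the main result. Name one sensitivity analysis that adds baseline Tanner stage, and report the two sets of genotype estimates side by side. State that a difference between them may reflect a mediated effect and should not be read as a correction for confounding.

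No new data are needed. The cost is up to 4 degrees of freedom in 1,500 children and one extra sensitivity analysis. The one real downside, a shift of estimand, arises only if the stage-adjusted model is made the main association analysis.

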#### Genetic analysis

Genomic DNA for all subjects is stored at -20°C after isolation from EDTA blood following a standard protocol. In a first step several SNPs were selected from HapMap CEU data (release 21 phase II, dbSNP 125) including SNPs with minor allele frequencies > 5% in genes of interest for the phenotypes available (e.g. body weight, physical fitness, risk factor profile). In a first step, genotyping was performed using the *MassARRAY *system with *iPLEX™ Gold *chemistry (*Sequenom*, San Diego, CA, USA). The samples were analyzed in a matrix-assisted laser desorption ionisation time of flight mass spectrometer (*MALDI TOF MS, BrukerDaltonik*, Leipzig, Germany). Further analyses will be performed using state of the art genotyping methods.

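### The primary gene question spans at least three genes and two unranked outcomes at α = 0.05, with correction only among genotype pairs, so its family-wise error is about 14% to 27%, not 5%

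*Protocol article*

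**What the plan says.** All references are to the Methods/Design part of the protocol article.

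- **Outcomes.** The Primary endpoint section concerns genetic associations "on the changes in BMI and BMI-SDS after a controlled lifestyle intervention (4 to 6 weeks"). Both outcomes are primary and neither is ranked above the other.
- **Genes, as the endpoint is defined.** The same section refers to "polymorphisms in adiposity-relevant genes (e.g. *FTO, MC4R, TMEM-18", so the list there is given by example.
- **Genes, as the analysis is defined.** The Statistical considerations section repeats the three genes without that qualifier: "FTO, MC4R, TMEM-18*) and changes in BMI(-SDS) from the start to the end of the intervention". Three is therefore the minimum.
- **SNPs.** The Genetic analysis section says "In a first step several SNPs were selected from HapMap CEU data". It gives no number and mentions several phenotypes, not only body weight.
- **Primary test.** ANCOVA "comparing mean changes in BMI(-SDS) between the two groups of homozygous and the group of heterozygous children", which is a 2-degree-of-freedom test per SNP and outcome.
- **Levels.** For the ANCOVA: "A two-sided level of significance of α = 0.05 will be used". For the genotype pairs: "two-sample t-tests will be conducted using a Bonferroni-adjusted level of significance of α* = 0.0167". The sample size paragraph confirms that 0.0167 refers to comparisons between allele groups.
- **Status.** Only the middle- and long-term gene analyses are described as explorative.

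**The concern.** The plan corrects for one source of multiplicity, the three genotype pairs within a gene, and leaves two others uncorrected: the number of genes and the two outcomes. Because only the later analyses carry the explorative label, the short-term gene tests read as the confirmatory part of the study.

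Under the plan as written, one nominally significant gene-outcome pair could be reported as a primary finding at the 5% level, although the chance of at least one such finding under no effect is several times 5%. This bears on the study's main purpose. The Discussion says that earlier paediatric studies of genes and weight change during lifestyle intervention were fairly small and disagreed with each other, and it presents the larger sample here as the way to settle such questions. An inflated error rate weakens that case.

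**Working it through.** **1. The plan's own figures.** Inputs from Statistical considerations: 1,500 children; genotype split 70/25/5%, i.e. 1,050, 375 and 75; difference 0.5 SD; α* = 0.05/3 = 0.0167.

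Two-sample t-test, two-sided at 0.0167, noncentrality 0.5/√(1/375 + 1/75) = 3.95:
- 375 versus 75: power 93.9% (94.1% by the normal approximation)
- 1,050 versus 75: power 96.3%

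The comparison of 1,050 with 375 has more power still. The stated power above 90% and the value of α* reproduce, so the arithmetic is not the problem.

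**2. Family-wise error of the primary ANCOVAs.** Assumptions the article does not supply: one SNP per gene, the three SNPs independent, no true effect anywhere, every ANCOVA at 0.05.

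- Outcomes perfectly correlated (three tests in effect): 1 − 0.95³ = 14.3%
- Outcomes independent (six tests): 1 − 0.95⁶ = 26.5%

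For correlations in between, 2-df tests on two outcomes were simulated (2 million draws each). If p is the chance that at least one of a gene's two tests is significant, the three-gene figure is 1 − (1 − p)³:

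| Assumed correlation of BMI and BMI-SDS change | p per gene | Three genes |
|---|---|---|
| 0.5 | 9.1% | 25.0% |
| 0.7 | 8.4% | 23.2% |
| 0.8 | 7.9% | 21.9% |
| 0.9 | 7.1% | 19.9% |
| 0.95 | 6.5% | 18.3% |

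If the primary list had four independent SNPs, the range would be 18.5% (1 − 0.95⁴) to 33.7% (1 − 0.95⁸).

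**3. Does the 0.0167 correction rescue this?** Take the pairwise tests alone, run without a preceding global test. Simulation at 1,050/375/75 gives about 4.0% for at least one false positive per gene and outcome. Over three genes with one outcome: 1 − (1 − 0.040)³ = 11.5%. The correction holds 5% within one gene and outcome, but not over the family.

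**4. Check of the proposed rule.** One outcome, global test at 0.0167 per gene, then pairwise contrasts at 0.0167 only after a significant global test. Simulated error per gene is about 1.7% with all three groups equal, and also when any one group differs from the other two. Three genes give at most about 3 × 1.67% = 5%.

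Power at 1,050/375/75:

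| Pattern | Global at 0.05 | Global at 0.0167 | 375 v 75, ungated | 375 v 75, gated |
|---|---|---|---|---|
| Minor homozygotes shifted 0.5 SD, other two groups equal | 97.3% | 93.3% | 94.0% | 91.5% |
| 375 v 75 differ by 0.5 SD, major homozygotes at their weighted mean (0.5 × 75/450 = 0.083 SD from the heterozygotes) | 95.2% | 89.2% | 94.0% | about 89% |

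For comparison, plain Bonferroni without a gate over three genes and three pairs (0.05/9 = 0.0056) gives 87.8% for 375 versus 75. Over two outcomes as well (0.05/18 = 0.0028) it gives 82.7%.

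**The case against.** - **The analysis plan is not shown.** This is an observational cohort described in a condensed article, and a rule across genes or a ranking of outcomes could sit elsewhere. That stands as a caution. But the article does not leave multiplicity open: it states the levels, chooses a correction and bases its power on it. The point is that the stated rule falls short, not that detail is missing.
- **The text does not say that each ANCOVA is tested at 0.05, nor that the analysis is confirmatory.** Both are inferences. They are the natural reading, because one level is given for the models with no division, and only the later analyses are called explorative.
- **A reader might infer that the error is at least 20%.** That needs a correlation between the outcomes of about 0.9 or lower, which the article does not give. At 0.95 the figure is 18.3%, and the floor is 14.3%.
- **A reader might infer a much larger figure from the several SNPs genotyped.** The number is not stated, and the SNPs were chosen for several phenotypes, so they cannot all be counted as primary tests. The analysis section also lists three genes without the qualifier used in the endpoint definition.
- **A reader might infer that the 0.0167 correction is misplaced**, since three groups need no further adjustment after a significant global test. The plan states no such gate. Ungated, the three t-tests do need adjustment, and 0.05/3 is valid.

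**Conclusion.** The point holds. The primary question covers at least three genes and two unranked outcomes, the ANCOVA level is 0.05, and the only correction applies within one gene and outcome. For three independent SNPs, one per gene, the chance of at least one false-positive primary ANCOVA lies between 14.3% and 26.5%, depending on a correlation the article does not report. Even the lower end is nearly three times the nominal 5%. The figure rises if more SNPs enter the primary analysis, but the article gives no basis for saying how far. The sample size calculation is internally correct and is not in question.

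**What to change.** Change the Primary endpoint and Statistical considerations sections as follows:

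1. Name one of the two outcomes as primary, for example change in BMI-SDS, with the other supportive.
2. Close the primary list at one named SNP in each of FTO, MC4R and TMEM-18, and word the gene list the same way in both sections.
3. Test each SNP's global ANCOVA at 0.05/3 = 0.0167. Only if it is significant, test that SNP's three pairwise contrasts at 0.0167.
4. Label all further SNPs exploratory.

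Change in BMI-SDS is only an example, and other valid schemes exist. This one keeps the pairwise threshold already in the plan and loses less power than plain Bonferroni over genes and pairs.

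No extra children or measurements are needed. The cost is some power: with only the minor homozygotes shifted by 0.5 SD, the global test falls from 97.3% to 93.3% and the 375-versus-75 comparison from 94.0% to 91.5%. If the major homozygotes lie between the other two groups, gated pairwise power can be about 89%. The statement that every pairwise comparison has more than 90% power should therefore be limited to the pattern for which it holds, or lowered slightly.
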